# Evaluation of the PhunkyFoods intervention on food literacy and cooking skills of children aged 7–9 years: a cluster randomised controlled trial in Yorkshire Primary Schools UK

**DOI:** 10.1186/s13063-022-06558-5

**Published:** 2022-08-01

**Keywords:** Cluster RCT, Food literacy, Cooking skills, Complex intervention, Childhood obesity prevention, Primary schools, Protocol

## Abstract

**Background:**

Childhood obesity rates more than double during primary school in England. Acquiring competent cooking skills is a key part of children’s education that can lead to improved knowledge of a healthy lifestyle and dietary behaviours. Evaluation of the impact of ‘PhunkyFoods’, a school-based food and nutrition education programme, will assess food literacy, cooking skills and dietary behaviour in primary-school children.

**Methods:**

A cluster randomised controlled trial will be undertaken in 28 primary schools in North Yorkshire, UK, including a total population of children aged 7–9 years (*n* = 420). The trial has two arms: (a) the intervention group receiving PhunkyFoods programme (*n* = 210) and (b) the wait-list control group receiving the usual school curriculum (*n* = 210). The intervention ‘PhunkyFoods’ will be delivered by Purely Nutrition Ltd. The participating school staff are supported with training, policy development and access to resources to improve the delivery of nutrition education. Children participate through whole school assemblies, classroom activities, and after-school clubs about food preparation, cooking healthy meals and healthy living. Schools, parents and children have access to healthy meal recipes through the PhunkyFoods website. The primary outcomes are differences in food literacy and cooking skills scores between control and intervention arms after 12 months of the intervention and adjusted for baseline values. The secondary outcome is differences in fruit and vegetable intake between the arms after 12 months (adjusted for baseline). Treatment effects will be examined using mixed ANOVA and regression analysis. Primary analyses will adjust for baseline food literacy and cooking skills scores and secondary analysis will adjust for pre-specified baseline school and child level covariates.

**Discussion:**

The PhunkyFoods programme is a flexible menu of options for schools to choose from, making this a highly complex intervention. Following Medical Research Council guidance, research perspectives will focus on effectiveness and theory-based approaches: to what extent the intervention produces the intended outcomes in real-world settings and what works in which circumstances.

**Trial registration:**

ISRCTN ISRCTN68114155. Prospectively registered on 22 October 2021

**Supplementary Information:**

The online version contains supplementary material available at 10.1186/s13063-022-06558-5.

## Administrative information

Note: The numbers in curly brackets in this protocol refer to SPIRIT checklist item numbers. The order of the items has been modified to group similar items (see https://uk01.l.antigena.com/l/No6NZkdmCCqK54rxvBrmWWdkRMJMZezCpgvwMZggQBsXfTE5JxwRkvfLlKx0U70lwk7cMxP4G-JXA9DRXoSHskRP35mvo0zLdHo13fmjz3NUC2JsGZx7J2EDnMtOmO38H5AIbd3MRNSKY9lc58ocvVAIu9e8SKQUoh9njrlxFgTyLFNTJYXVHyGkSTxrbtVR3WJgqPGboeXzZpCi3bHGJTQ6-boK).

## Introduction

### Background and rationale {6a}

#### Childhood obesity in the UK

Childhood obesity rates typically double during primary school in England and prevalence at age 4–5 years in reception classes has increased to 14% in 2020/2021 [1]. Good nutrition and maintaining a healthy weight in childhood help to prevent obesity and diet-related ill health later in life [2]. Knowledge about nutrition and cooking healthy meals helps people to live healthier lives [3–5].

#### School-based nutrition programmes: existing knowledge

A systematic literature review of successful primary school-based nutrition programmes has highlighted the value of experiential curriculum strategies to develop food literacy and cooking skills in children. Programmes are more likely to be successful if they have multiple strategies, parental involvement and focus specifically on vegetable intake [6].

The PhunkyFoods programme aims to help early years settings and primary schools to deliver a whole-settings approach to healthy lifestyles and to engage with all pupils, and their families, in promoting tangible health behaviour change in a fun, lively and positive manner. The cooking skills elements of the PhunkyFoods programme delivered in schools are supplemented with additional components such as online videos demonstrating knife and other cooking skills [7].

The feasibility study undertaken in 2019 by Sahota and colleagues [8] identified key outcomes of the programme but was not powered to detect definitive effectiveness. However, results did show the potential of the programme to increase knowledge of healthy lifestyle and dietary behaviours.

This research will build on the previous feasibility trial by implementing recommendations for enrolment and baseline data collection with a fully powered phase 3 trial design. The trial will investigate the impact of the PhunkyFoods programme on dietary behaviour, nutrition knowledge and cooking skills for primary-aged children aged 7–9 years. This age group was chosen as relevant for study as this population is also targeted by the World Health Organization Child Obesity Surveillance Initiative (COSI) as an important area for research. This UK trial will provide supplementary contextual data to complement the current COSI survey 2021–2023, which includes new questions about children’s food preparation and cooking skills in this age group [9].

### Objectives {7}

The main aim is to assess the impact of the PhunkyFoods healthy lifestyle intervention programme, (developed and refined by Purely Nutrition), on food literacy, cooking skills and fruit and vegetable intake of children using usual practice in primary schools as the comparator. Intervention effects will be examined at 12 months. The cost-effectiveness of the intervention will be assessed from a societal perspective. In addition, differences in outcomes will be explored by model fidelity in each school setting, other healthy living initiatives in the local area and socioeconomic status using percentage eligibility for free school meals (%FSM) and the index of multiple deprivation (IMD) as covariables.

The PhunkyFoods programme is a flexible menu of options for schools to select from, making this a highly complex intervention. Following the Medical Research Council guidance on the evaluation of complex interventions, research perspectives will focus on effectiveness and theory-based approaches: the overall objective of the study is to explore to what extent the intervention produces the intended outcomes in real-world settings and what works in which circumstances [10].

The research hypotheses are as follows:The PhunkyFoods intervention group will show higher food literacy and cooking skills than the control group measured by mean scores.The PhunkyFoods intervention group will show a higher intake of fruit and vegetables than the control group measured by mean scores.Schools in the intervention arm that choose more ‘active ingredients’ (intervention components) from the flexible menu of options will have better outcomes than those schools that choose less ‘active ingredients’.The covariates, %FSM and IMD, will have a mediating impact on the outcomes for schools in the intervention arm.

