### Assignment of interventions: allocation

#### Sequence generation {16a}

A computer-generated randomisation sequence will be used to allocate schools into the intervention and wait-list control arms of the trial. Block randomisation will be used to ensure equivalence between intervention and waitlist-control schools. Furthermore, schools will be stratified according to region (e.g. Selby or Harrogate) and whether they are above or below the England median for free school meals eligibility [19]. The randomisation will be conducted immediately after T1 baseline data is collected.

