### Methods for additional analyses (e.g. subgroup analyses) {20b}

Secondary analysis will use a theory-based approach to explore the interplay of mechanisms and context [10], including model fidelity. This will involve adjusting for pre-specified baseline school and child level covariates to investigate the impact of the intervention arm for individual clusters. Multiple regression will be used with the number of intervention components as a predictor variable. In addition, %FSM and IMD will be used in a linear model as predictor variables. The study will have low power to detect all but the largest differences in subgroups.

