## Discussion

The World Health Organization (WHO) Regional Office for Europe Data Dashboard shows that obesity continues to rise at an alarming rate [21]. The global target of halting the rise of obesity is going in the wrong direction in the WHO European Region and so effective interventions to improve diet quality are needed. The overall findings from the fourth round of the WHO COSI report showed that almost 1 in 3 children aged 6–9 are living with overweight or obesity. The highest prevalence of childhood overweight and obesity were observed in Cyprus, Spain, Greece and Italy, where over 40% of boys aged 6–9 years and over 30% of girls aged 6–9 years were living with overweight (including obesity) [22]. The PhunkyFoods intervention could be a UK case study example that could inform similar interventions in other Member States.

Given the complex nature of the intervention and the contextual factors, it will not be possible to examine the efficacy of the PhunkyFoods programme as an experimental setting. Instead, the research perspective focuses on effectiveness and theory-based approaches. The cluster randomised controlled trial design and plans for secondary analysis will allow for some investigation and discussion into what works in what circumstances and why.

The additional level of complexity for this study is the flexibility in which schools choose from the active ingredients in the Logic Model. Whilst this reflects the real-world context of the study, it also limits the statistical power for cluster comparison between settings since the intervention will likely look very different in each school. It is hoped that the secondary analysis using complex regression, using the number of active ingredients, %FSM and %IMD as predictor variables, combined with observations from the audit visits, will enable some discussion about the effectiveness of particular settings.

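### Hypothesis 4 calls %FSM and IMD mediators within the intervention arm; both are fixed before randomisation, so the question is effect modification, and no arm-by-covariate term is named to address it

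*Protocol article*

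**What the plan says.** The Objectives section of the protocol article lists four hypotheses. The fourth is: "The covariates, %FSM and IMD, will have a mediating impact on the outcomes for schools in the intervention arm". Earlier in that section the aim is put more broadly, as exploring outcome differences by several factors including "socioeconomic status using percentage eligibility for free school meals (%FSM) and the index of multiple deprivation (IMD) as covariables", with no restriction to one arm. The overall objective is to learn "to what extent the intervention produces the intended outcomes in real-world settings and what works in which circumstances".

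The matching analysis is in Methods for additional analyses {20b}: "In addition, %FSM and IMD will be used in a linear model as predictor variables". The Discussion restates it as regression "using the number of active ingredients, %FSM and %IMD as predictor variables". Neither place names an arm-by-covariate term, a contrast with control schools for this hypothesis, or a mediation model. Section 20b also speaks of adjusting for baseline school and child covariates, and it concedes low power for subgroup differences.

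Under Sequence generation {16a}, schools are stratified by region and by "whether they are above or below the England median for free school meals eligibility". On timing: "The randomisation will be conducted immediately after T1 baseline data is collected".

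**The concern.** A mediator lies on the path from treatment to outcome, so treatment must be able to change it. School %FSM is known when schools are allocated, and the programme has no route by which it could alter an area deprivation index. The sensible question, and the one that fits the overall objective, is whether the programme effect varies with deprivation.

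That question needs a treatment contrast at different levels of deprivation. Hypothesis 4 is framed within the intervention arm, where there is no contrast. The analysis text supplies predictors but no term for a varying effect. If scores, or changes in scores, simply differ by deprivation in all schools, a coefficient on %FSM could be taken as evidence that the programme works better or worse in deprived schools. That would be a misleading equity message from one of only four stated hypotheses.

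**Working it through.** The plan gives no figure for this analysis, so there is none to reproduce. The check has three parts.

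**1. What each coefficient estimates.** Let T be arm (0/1), F the standardised deprivation covariate and Y the outcome, baseline-adjusted or not:

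Y = b0 + b1·T + b2·F + b3·T·F + error

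- The slope in control schools is b2, the ordinary gradient.
- The slope in intervention schools is b2 + b3.
- With equal arms, the coefficient on F in a model without the product term is b2 + b3/2.
- Effect modification is b3.

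Neither the second nor the third quantity identifies b3 unless b2 is known. Baseline adjustment changes the meaning of b2, from a gradient in scores to a gradient in change, but does not make it zero.

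**2. Illustration.** School means were simulated for 14 + 14 schools, with an arm effect of 0.52 SD and school-mean variance 0.20 + 0.80/15 = 0.253 (ICC 0.20 and 15 children per school, from Sample size {14}). There were 4,000 runs, tested at two-sided 5%. The slopes per SD of F are assumptions; the documents give none. Cells show the mean estimate and the share of runs with p < 0.05.

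| Slope, control / intervention | True b3 | Intervention-arm slope | Pooled coefficient, no interaction | Interaction |
|---|---|---|---|---|
| −0.30 / −0.30 | 0 | −0.30 (50%) | −0.30 (81%) | 0.00 (5%) |
| 0 / −0.30 | −0.30 | −0.30 (48%) | −0.15 (28%) | −0.30 (27%) |
| +0.15 / −0.15 | −0.30 | −0.15 (16.5%) | 0.00 (6%) | −0.30 (28%) |

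The first two rows give the same intervention-arm slope and almost the same rejection rate, yet one has no modification and the other has a good deal. The third row shows a pooled coefficient missing modification altogether. Only the interaction tracks the truth in all three. The simulation contains no baseline score, so it shows the direction of the problem, not its likely size in this trial.

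**3. Precision of the interaction.** Inputs: 14 schools per arm, 15 children each (210 per arm), ICC 0.20, and an assumed even split of schools into high and low FSM. The protocol states no alpha for its power calculation; two-sided 5% is assumed.

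- Design effect: 1 + (15 − 1) × 0.20 = 3.8
- SE of the arm difference: √(2 × 3.8/210) = 0.190 SD
- SE of the interaction (difference between two half-sample effects): 2 × 0.190 = 0.380 SD
- Power for a 0.52 SD interaction: Φ(0.52/0.380 − 1.96) = Φ(−0.59) ≈ 0.28
- Smallest interaction detectable with 80% power: 0.380 × (1.96 + 0.842) ≈ 1.07 SD; with 90% power, 0.380 × (1.96 + 1.282) ≈ 1.23 SD
- 95% CI half-width: 1.96 × 0.380 ≈ 0.75 SD

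These figures take no credit for baseline adjustment, which could narrow the interval.

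**The case against.** The best defence is that the analysis text is less specific than the concern needs. Section 20b neither states nor excludes an interaction. It sits under a heading that mentions subgroup analyses and closes with a remark on power for subgroup differences, which is compatible with looking for differences in effect. A condensed article may also leave exact model terms to an analysis plan that is not shown.

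Much of this stands, and it rules out a stronger reading. A reader might infer that the trial will fit a main-effects model in intervention schools only and will therefore answer its question wrongly. The documents do not support that: a main-effects model is only an inference from the words predictor variables, and the restriction to intervention schools appears in the hypothesis, not in section 20b. The Discussion hopes only for some discussion, aided by audit visits, and the overall objective also covers the choice of components.

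It is also fair that a −0.30 SD gradient is assumed. If the secondary models adjust for baseline outcome scores, which the article does not say explicitly, a stable gradient would be partly absorbed. A gradient in change would remain confounded with modification.

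What the defence does not reach is the hypothesis itself. Even if mediating is loose wording for moderating, the question is posed in one arm, and an analysis faithful to that wording could not answer it.

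**Conclusion.** The point holds in a limited form. Hypothesis 4 gives pre-randomisation characteristics the wrong causal role and poses an effect-modification question within one arm. The analysis text names no term that would separate modification from an ordinary deprivation gradient, so the result could be misread as support for the hypothesis. This follows from the algebra and does not depend on the assumed slopes. How often a misreading would occur does depend on them, and cannot be fixed from the documents.

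The weight is moderate to low. This is a secondary analysis with its own caveat about power, and the primary comparison is untouched.

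**What to change.** - Reword hypothesis 4 so that it asks whether the programme effect differs by %FSM or IMD, across both arms.
- State in section 20b that arm × %FSM and, in a separate model, arm × IMD will be estimated using all schools in both arms, in a baseline-adjusted model that accounts for school clustering.
- Report each interaction with its 95% CI, labelled exploratory. A non-significant interaction should not be read as an equal effect across deprivation levels.
- Align the Discussion sentence with this.

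The cost is one hypothesis and one model line. No additional data collection is needed: outcomes are measured in both arms, FSM is already used for stratification, and IMD is already to be tabulated. The drawback is the imprecision shown above, which is consistent with the low subgroup power that section 20b already concedes.

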### Trial design {8}

The PhunkyFoods evaluation design is a parallel, cluster randomised controlled trial, with two arms and with a 1:1 allocation ratio. The intervention arm will receive the PhunkyFoods programme starting in May 2022, and the wait-list control arm will receive the PhunkyFoods programme after the final research data collection, with training from May 2023 (superiority trial). If the trial is not able to recruit 28 schools within the recruitment period, then the research team will consider an unequal allocation ratio with a smaller number of schools in the control group or widening the geographical recruitment area. The impact of this is discussed in the section on sample size.

## Methods: participants, interventions and outcomes

### Study setting {9}

All state mainstream primary schools in Harrogate (*n* = 74) and Selby (*n* = 40) areas of North Yorkshire are eligible for inclusion and will be invited to express an interest in the study. Schools will be approached until the required sample size of (*n* = 28) schools is achieved.

### Eligibility criteria {10}

The following are the exclusion criteria: schools with fewer than 20 pupils in the relevant year groups (year 3 and/or year 4); schools that are unable to commit to the two data collection points in March 2022 and March 2023 for the identified class of children will also be excluded from the study.

### Who will provide informed consent? {26a}

Informed consent will be requested at three stages:School consent: Headteachers will be provided with an information sheet and consent form for the Study. Details of the PhunkyFoods Programme and the research study will be explained via a 30-min School Briefing session on Microsoft Teams by the lead researcher (KV). If they decide to participate and the school meets the eligibility criteria, informed consent for the school to participate will be signed by the headteacher and a class identified to participate in the study.Parent consent: Once the school consent has been obtained, a parent information sheet will be sent out for all the parents/carers for children in the identified class with an opt-out clause. If parents do not want their child to participate in the research study, they can either email or ring the school. This information will then be passed to the research team to update the recruitment flow diagram. Parents will be given 2 weeks if they wish to withdraw their child from the research study. This will mean that all children will still participate, and no child will be excluded from the PhunkyFoods programme activities. This includes the data collection activities; however, their data will not be used for the purposes of research if the parent opted out.Child assent: The two data collection surveys for children will have a consent tick box on the front page. The lead researcher will explain that no individual child will be identified from the study, and the information will not be used beyond the research team. Children who are happy with the surveys to be used in the research study will be asked to tick the consent box on the front page of the surveys. At the beginning of the research activity, the researcher will explain to the children about the work of the University on Food Science and Nutrition and ask them to complete the surveys as part of the study.

### Additional consent provisions for collection and use of participant data and biological specimens {26b}

N/A—no biological specimens are collected as part of this trial.

### Interventions

#### Explanation for the choice of comparators {6b}

The control group schools will receive their usual existing school curriculum for food science as delivered in the Food Technology schemes of work, without any support from the PhunkyFoods Programme. This may include specific nutritional components, designed and delivered by the school. In the UK, the Department for Public Health sets out the topics that should be covered in Food Technology lessons for primary schools [11] but in reality, this is likely to look different across school settings. We will ensure we collect relevant information on what schools are currently doing in relation to food knowledge and skills and include this information in the analysis as an additional independent variable if deemed appropriate.

#### Intervention description {11a}

The PhunkyFoods Programme is a flexible menu of 8 ‘active ingredients’, which schools can select from. The Education Endowment Foundation (EEF) uses the term ‘active ingredients’ to describe intervention components in a school intervention [12]. The PhunkyFoods Logic Model in Additional file 1 shows the behaviour theory for the PhunkyFoods programme and implementation planning.

The PhunkyFoods programme has a detailed delivery manual with implementation guidance and resources for Engagement & Development Coordinators (EDCs) to deliver each of the 8 active ingredients in partnership with schools [13]:Active ingredient 1: Whole setting staff training in the PhunkyFoods Programme with additional Continuous Professional Development (CPD) opportunities available for schools to opt into. Examples of CPD opportunities include National Level 2 Award in Nutrition and Health of School Aged Children, Food Prep in the Classroom and Setting Up and Running a Cook Club.Active ingredient 2: Whole Setting Audit (Health Check) and action planning support around the Whole School Approach to Health. This consists of an initial meeting with a member of the Senior Leadership Team (SLT) to work through the Health Check document, then co-production of an action plan for development priorities agreed.Active ingredient 3: Policy evaluation and updating of Whole School Food and Packed Lunch policies.Active ingredient 4: Whole school activities such as assemblies and pupil workshops on a range of topics relating to Phunky FOOD. Examples include Eatwell, Strive for 5, Drain your Drinks, Bag-A-Breakfast, Top Teeth, A Healthy Lunch, Snack Attack, Food Waste, Phunky FIT (Get Active) and Phunky MINDS (Resilience, Feelings, Relationships, Anti-Bullying).Active ingredient 5: Experiential curriculum/classroom-based activities. Examples include Design and Technology Scheme of Work; Personal Health and Social Education Scheme of Work; Topic Based Activities; Planning, Preparation and Assessment solutions (healthy eating and physical activity); Phunky15 (physical activity); and Mindful Moments.Active ingredient 6: Extra-curricular activities. Examples include Breakfast Club, Cookery Club, Gardening Club and After-schools Club.Active ingredient 7: Student-led activities. The Phunky AMBASSADORS programme involves mentoring students to deliver key healthy lifestyle messages through peer-to-peer learning.Active ingredient 8: Parent engagement activities. Examples include Parent/Child Cook Clubs, Parent Workshops, Parent Stay and Play Sessions, Parent Health Promotion Events and Parent Communication Material (newsletter text; email snippets; display assets).

